### Trial endpoints

NT-proBNP is used widely to monitor the therapeutic efficacy of agents for heart failure in clinical trials and is established as a prognostic biomarker for heart failure [21–23]. In addition, NT-proBNP-guided treatment for heart failure has been demonstrated to improve clinical outcomes in a randomized trial [24]. Therefore, the percent change in NT-proBNP levels from baseline to 24 weeks will be used as the primary endpoint in the CANDLE trial. The secondary endpoints are the values and changes in parameters after 24 weeks of treatment (or at discontinuation), including: (1) NT-proBNP, (2) glycemic control (HbA1c, fasting plasma glucose, plasma insulin, HOMA-R and HOMA-beta), (3) clinic systolic and diastolic BP and home BP (optional), (4) BW, (5) biochemical tests (lipid profiles and uric acid), (6) quality of life (MLHF scores) (7) echocardiographic cardiac function parameters (LVEF and E/e’) and severity and change in NYHA functional classification, and (8) renal function parameters (serum creatinine level, estimated glomerular filtration rate (eGFR), urinary albumin excretion, and urine L-FABP). Other secondary endpoints include clinical outcomes such as CV events, including all-cause death, non-fatal myocardial infarction, non-fatal stroke, hospitalization for heart failure, and changes in medications related to aggravation of heart failure. Safety endpoints include adverse effects and adverse drug reactions observed during treatment with the study drugs. The exploratory endpoints are changes in specific biomarkers after 24 weeks of treatment, including high-sensitivity troponin I, hsCRP, serum cystatin C, PTX3, RAGE, ANGPTL2, IL-8, and periostin. The findings of these biomarker assays may, in part, provide mechanistic insights on the effect of canagliflozin on CV pathogenesis.

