## Abstract

**Background:**

Because type 2 diabetes mellitus is associated strongly with an increased risk of cardiovascular diseases, the number of patients with diabetes with chronic heart failure is increasing steadily. However, clinical evidence of therapeutic strategies in such patients is still lacking. A recent randomized, placebo-controlled trial in patients with type 2 diabetes with high cardiovascular risk demonstrated that the SGLT2 inhibitor, empagliflozin, reduced the incidence of hospitalization for heart failure. Because SGLT2 inhibitors cause a reduction in body weight and blood pressure in addition to improving glycemic control, they have the potential to exert beneficial effects on the clinical pathophysiology of heart failure. The aim of the ongoing CANDLE trial is to test the safety and non-inferiority of canagliflozin, another SGLT2 inhibitor, compared with glimepiride, a sulfonylurea agent, in patients with type 2 diabetes mellitus and chronic heart failure.

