### Randomization and treatment

Eligible patients with the appropriately signed informed consent will be randomized to either the canagliflozin or glimepiride groups at a ratio of 1:1 using the minimization method with biased coin assignment balancing for age (<65, ≥65 year), HbA1c level (<6.5, ≥6.5 %), and left ventricular ejection fraction (LVEF; <40, ≥40 %) at the time of screening [18, 19]. The trial is an open-label design, although the assessor(s) will be blinded to treatment randomization. The assessors will also be blinded to the primary end point, NT-proBNP level, by measurement at a central laboratory.

All participants receive the study drug for 24 weeks. Patients who are assigned to the canagliflozin group receive canagliflozin 100 mg once daily. The EMPA-REG OUTCOME trial reported small dose-dependent effects of empagliflozin (10 mg vs. 25 mg/day) on metabolic parameters. However, the two dose groups had similar hazard ratios for cardiovascular outcomes [13]. Some studies on canagliflozin showed that 100 mg/day had sufficient effects on metabolic parameters, while 300 mg/day was slightly more effective [14, 15, 20]. Importantly, only 100 mg/day is approved in Japan, and therefore the dose of canagliflozin is fixed at 100 mg/day in the canagliflozin group. Because of the possible risk of excess diuresis and subsequent dehydration by combined use of canagliflozin and diuretics, the dose of the diuretics may need to be reduced when necessary. Patients assigned to the glimepiride group are started at a dose of 0.5 or 1.0 mg once or twice daily. According to the individual’s glycemic control, the dose of glimepiride can be increased to 6.0 mg/day. For background therapy in both groups, participants who have been receiving any SGLT2 inhibitor other than canagliflozin need to discontinue it at the start of the washout period, for 4 weeks, prior to receiving the study drug, canagliflozin or glimepiride. While, participants who have been taking a sulfonylurea need to stop taking it in the canagliflozin group and need to change to glimepiride (if needed) in the glimepiride group at the initiation of the study drug (Additional file 1). Because of the possible risk of excess diuresis and subsequent dehydration by combined use of canagliflozin and diuretics, the dose of the diuretics may need to be reduced when necessary.

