### Measurements

Baseline characteristics, including smoking habit, NYHA functional classification, etiology of CHF, hypertension, dyslipidemia, and other complications will be screened prior to randomization. The medication status of the study agents, and the participant’s background treatment, BW, BP, and heart rate will be also measured at each visit. A chest X-ray is taken at baseline and at the final visit. An echocardiogram is performed at screening, baseline, and the final visit to measure LVEF using the modified Simpson method and E/e’. The echocardiograms will be evaluated by technicians at each local site. Blood and urine tests will be checked at each visit (details listed in Additional file 3). Specific biomarkers, including NT-proBNP, high-sensitivity C reactive protein (hsCRP), serum cystatin C, pentraxin 3 (PTX3) (SRL, Inc. Tokyo, Japan), high-sensitivity troponin I (Abbot Japan, Tokyo, Japan), receptor for advanced glycation end products (RAGE), angiopoietin-like protein 2 (ANGPTL2), interleukin 8 (IL-8), and periostin (Saga University) will be measured at a central laboratory at baseline and the final visit. CHF-related quality of life is evaluated by scaled responses to the Minnesota Living with Heart Failure (MLHF) questionnaire at baseline and the final visit. The occurrence of CV events, including all-cause death, non-fatal myocardial infarction, non-fatal stroke, hospitalization for heart failure, and additional medications or dosage increases of drugs due to aggravation of heart failure will be evaluated.

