### Safety

Based on the intention-to-treat entire population, safety will be checked by recording the following adverse effects throughout the duration of the study: hypoglycemia, genital infections, urinary tract infections, excess osmotic diuresis signs (increased urinary frequency, mouth dryness, or polyuria), and hypovolemic symptoms. A previous study has reported an increased prevalence of hypoglycemia with sulfonylureas than with canagliflozin [14]. We therefore need to pay careful attention to the development of hypoglycemia, especially in patients assigned to the glimepiride group, despite this drug being initiated at a low dose in the study. If the investigators confirm these adverse effects, the grade of severity, treatment, outcomes, and relationship to the study drug will be assessed. The criteria for withdrawal from the trial are listed in Table 3. In addition, the incident of withdrawal from the study will be reported promptly to the Data and Safety Monitoring Board (DSMB) by the trial organizer.

**Table 3 Tab3:** Discontinuance criteria

Severe hypoglycemia that needs some support by family members or medical care at medical settings
Seriously poor glycemic control such as ≥HbA1c 10.0 %
Diabetic ketoacidosis
Dehydration
Considered inappropriate to continue the study by investigators due to aggravation of primary disease or complications
Considered inappropriate to continue the study by investigators due to adverse side effects of the study drug
Offer for participation declined by participants
Considered inappropriate to continue the study by investigators due to some other reason

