### Statistical considerations

#### Sample size estimation

Due to the lack of data on the effect of SGLT2 inhibitors, including canagliflozin, on NT-proBNP levels, we used data from the PARAMOUNT study on CHF patients with preserved ejection fraction [25]. That study used the same primary end point to compare the efficacy and safety of LCZ696, an angiotensin receptor neprilysin inhibitor, with valsartan. On the basis of the findings of that study, we assumed an 18 % difference in NT-proBNP reduction between the two groups in our trial. In detail, estimation of the sample size for the CANDLE trial was based on the percentage change from baseline to the final NT-proBNP level, required to demonstrate non-inferiority of canagliflozin versus glimepiride, using a one-sided Student t test with a 2.5 % type I error. In this calculation we assumed that for a common standard deviation for the log-scale of the ratio of 0.80, a clinical non-inferiority margin of 1.1, and a dropout rate of 10 %, it was necessary to recruit 125 patients in each group in the full analysis set (FAS) to demonstrate non-inferiority if the true difference was 18 % and the power was at least 80 %.

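### Secondary endpoints let a value taken at discontinuation stand in for the week-24 value, although stopping can be triggered by those same endpoints and for reasons expected to differ by arm

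*Protocol article*

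**What the plan says.** **Secondary endpoints** (Trial endpoints): "The secondary endpoints are the values and changes in parameters after 24 weeks of treatment (or at discontinuation"). The list includes NT-proBNP, HbA1c, blood pressure, body weight, quality of life, echocardiography and renal function.

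**Primary endpoint** (same section): "the percent change in NT-proBNP levels from baseline to 24 weeks will be used as the primary endpoint". No discontinuation alternative is attached. The exploratory biomarkers in that section, and the key secondary endpoints in the abstract, are also placed at 24 weeks without one.

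**Stopping** (Safety): "The criteria for withdrawal from the trial are listed in Table 3". Table 3 includes "Seriously poor glycemic control such as ≥HbA1c 10.0" %, and also dehydration and severe hypoglycemia.

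**Expected reasons by arm.** Randomization and treatment gives a warning for one arm: "Because of the possible risk of excess diuresis and subsequent dehydration by combined use of canagliflozin and diuretics". The Safety section asks for particular attention to hypoglycemia in the glimepiride group.

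**Analysis** (Analysis plan): the full analysis set admits treated patients without a serious violation who have some data after treatment began. Secondary endpoints are analyzed in the same way as the primary, by ANCOVA.

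**The concern.** A reading taken at any time after the first dose is analyzed beside true week-24 readings as if it were one of them. This would do little harm if stopping were unrelated to the endpoint, but here it is related in two ways.

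- **HbA1c.** A value of 10.0 % or more is both a reason to withdraw and a secondary endpoint, so the value that enters is likely to be the one that caused the stop. Patients who stop early for other reasons supply an HbA1c before the drug effect has had time to develop.
- **Body weight and blood pressure.** Dehydration can lower both. The abstract's background presents lower values as a favorable drug action: "Because SGLT2 inhibitors cause a reduction in body weight and blood pressure in addition to improving glycemic control". A canagliflozin patient withdrawn for dehydration can therefore add to an apparent benefit on these endpoints, and possibly on NT-proBNP.

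Because the expected reasons differ by arm, the error need not cancel between arms. It also does not shrink as the sample grows. At stake are the between-arm comparisons of blood pressure, weight and HbA1c that will be read alongside the primary result. In addition, one marker, NT-proBNP, has two time points in one section.

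**Working it through.** The plan gives no figure for this point, since it does not say how many patients are expected to stop for each cause. It supplies only two inputs.

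**Inputs from Sample size estimation:** 125 patients per arm and 10 % dropout. 125 x 0.10 = 12.5, so about 12 patients per arm for all causes together.

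**Assumed inputs (not in the article):** at the stop, systolic pressure 15 mmHg lower, weight 2 kg lower, HbA1c 2 points higher (10 % in place of 8 %), or log NT-proBNP 0.5 lower than the same patient would have had at week 24.

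**Formula:** shift in an arm mean = (number stopped / 125) x (value at stop - value otherwise expected at week 24). This equals the bias in the between-arm difference if the other arm has no such stops. If it has some, the bias is the difference between the two arms' shifts.

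| Stopped for one cause | Share | Systolic BP, -15 mmHg | Weight, -2 kg | HbA1c, +2 points | log NT-proBNP, -0.5 |
|---|---|---|---|---|---|
| 1 | 0.008 | -0.12 | -0.016 | +0.016 | -0.004 |
| 3 | 0.024 | -0.36 | -0.048 | +0.048 | -0.012 |
| 6 | 0.048 | -0.72 | -0.096 | +0.096 | -0.024 |
| 12 | 0.096 | -1.44 | -0.192 | +0.192 | -0.048 |

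With larger assumed deviations and 6 stopped, 20 mmHg gives 0.048 x (-20) = -0.96 mmHg and 3 HbA1c points give 0.048 x 3 = +0.14. The rows for 6 and 12 need about half, or nearly all, of the planned dropout to have that single cause.

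**Scale for NT-proBNP:** with the plan's log-scale SD of 0.80, the standard error of the difference is 0.80 x sqrt(2/125) = 0.101. The 6-patient shift is 0.024 / 0.101 = 0.24, about a quarter of one standard error.

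**Direction by cause:**

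- Dehydration on weight and blood pressure: harm looks favorable.
- Dehydration on NT-proBNP: possibly the same, but the article does not state this link.
- Dehydration on creatinine and eGFR: any worsening counts as harm.
- HbA1c stop on HbA1c: harm counts as harm, but a reading from an earlier time is labeled week 24.

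**The case against.** **The effect is small and assumed.** This stands. No stop counts by cause are given, and six patients for one cause is already about half of the planned dropout.

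**The timing of the at-stop reading is not stated.** This stands in part. For HbA1c it follows almost directly that the triggering value is used. For dehydration the reading could be taken after recovery, so capture at the extreme is an inference.

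**The harm is not hidden.** True. Hypovolemic symptoms and hypoglycemia are recorded as safety data, and withdrawals go to the data and safety monitoring board. That does not remove the distortion from the weight and blood pressure comparisons.

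**Missing-data handling belongs in the analysis plan.** Generally so, but here the article states a rule, and it is part of the endpoint definition.

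Three stronger readings are tempting, and the document supports none of them.

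- *Harm counts as benefit throughout.* It does not. A patient stopped for high HbA1c enters as a poor HbA1c result, and any renal effect of dehydration would count against the drug.
- *The primary result is affected.* The primary endpoint carries no discontinuation alternative. Setting the 0.024 log shift against the margin ln(1.1) = 0.095 therefore misapplies a margin that belongs to the primary.
- *The sample-size section gives a further time point.* It refers to "percentage change from baseline to the final NT-proBNP level". Scheduled follow-up ends at week 24, and under Measurements NT-proBNP "will be measured at a central laboratory at baseline and the final visit", so that wording reads naturally as the week-24 visit.

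**Conclusion.** The point holds for the secondary endpoints only. The stated definition treats at-stop readings from any earlier time as week-24 results, stopping depends on some of the same variables, and the expected reasons differ by arm. A harmful event can look favorable only for dehydration on weight and blood pressure, and possibly on NT-proBNP. Secondary and primary NT-proBNP also have different time points within one section.

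The size is probably modest. With 6 of 125 in one arm stopped for one cause, that arm's mean shifts by about -0.7 mmHg systolic, -0.1 kg or +0.10 HbA1c points. The shifts are proportionally smaller with 1 to 3 stops and double with 12. These figures rest on assumed stop counts and deviations, on at-stop readings taken before recovery, and on few such stops in the other arm. The primary endpoint and the sample size are not affected. The definition should still be changed, because the distortion is foreseeable and cheap to avoid. Nothing here bears on which stopping criteria are clinically right.

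**What to change.** 1. In Trial endpoints, define every secondary endpoint at week 24 and remove the discontinuation alternative.
2. For endpoints measured at each visit (body weight, blood pressure, and blood and urine tests where the schedule provides them), estimate the week-24 difference from a repeated-measures model over weeks 4, 12 and 24. Enter any at-stop reading at its actual time, not as a week-24 value. Keep it in the model, because it carries the information on why the patient stopped and so supports the missing-data assumption.
3. Give secondary NT-proBNP the same week-24 time point as the primary.
4. Report at-stop values separately, by arm and by reason for stopping.
5. NT-proBNP, the quality-of-life score and echocardiography have no interim value after baseline, so the model cannot recover them. Keep the at-stop version there as a labeled sensitivity analysis.

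**Cost:** changes to endpoint and analysis wording, with no new visit or sample. The downside is fewer values for the endpoints in item 5. The model also assumes that missing week-24 values are explained by the observed data. Which laboratory tests have week-4 and week-12 values should be checked against the measurement schedule in Additional file 3, which is not shown.

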#### Analysis plan

The analyses of the primary and secondary endpoints will be performed in the FAS, which includes all patients who received at least one dose of treatment during the study period and did not have any serious violation of the study protocol, and had data collected after commencement of treatment. For the baseline characteristics, the summary statistics will comprise frequencies and proportions for categorical variables, and means and standard deviations for continuous variables. The patient characteristics will be compared using Chi square tests for categorical variables, and t tests for normally distributed continuous variables or Wilcoxon rank sum tests for continuous variables with a skewed distribution.

For the primary analysis comparing treatment effects, the least square mean and its 95 % confidence interval will be estimated using analysis of covariance (ANCOVA). To test for non-inferiority of the primary endpoint, the ANCOVA will be applied adjusted for age (<65, ≥65 year), HbA1c level (<6.5, ≥6.5 %), and left ventricular ejection fraction (LVEF; <40, ≥40 %). The secondary analysis will be performed in the same manner as the primary analysis.

All comparisons are planned and all *p* values will be two sided. *P* values <0.05 will be considered statistically significant. All statistical analyses will be performed using SAS software version 9.4 (SAS Institute, Cary, NC, USA). The statistical analysis plan will be developed by the principal investigator and a biostatistician before completion of patient recruitment and database lock.

Trial organization and oversight (details in Additional file 4).

Principal investigators of the CANDLE trial are [name] (Chief), Department of Cardiovascular Medicine, Saga University and [name], Department of Cardiology, Nagoya University Graduate School of Medicine. The Steering Committee will carry out planning, operating, analyzing, and presentation of the trial. The Executive Committee will supervise the trial design and operation of the study. The roles of DSMB and CEC are described in the section of Endpoint adjudication. The trial secretariat is in DOT INTERNATIONAL CO., LTD, Tokyo, Japan. Each of data management, monitoring, statistical analyses, and audit will be independently implemented on the basis of outsourcing agreement.

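### Secondary parameters are endpoints both as 24-week value and as change, and without each parameter's own baseline in the ANCOVA these are two different tests; adding that baseline is a free improvement

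*Protocol article*

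**What the plan says.** All references are to the protocol article.

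- **Trial endpoints.** "The secondary endpoints are the values and changes in parameters after 24 weeks of treatment". The list continues "or at discontinuation), including: (1) NT-proBNP, (2) glycemic control", then blood pressure, body weight, biochemistry, quality of life, echocardiography and renal function. NT-proBNP is thus a secondary parameter, although "the percent change in NT-proBNP levels from baseline to 24 weeks will be used as the primary endpoint". The exploratory biomarkers are listed as changes only.
- **Abstract, Methods.** The key secondary endpoints are described as change from baseline in glycaemic control, blood pressure, body weight, lipids, quality of life, and cardiac and renal function. Values are not mentioned.
- **Analysis plan.** The ANCOVA is "adjusted for age (<65, ≥65 year), HbA1c level (<6.5, ≥6.5 %), and left ventricular ejection fraction (LVEF; <40, ≥40" %), that is, three two-level factors. "The secondary analysis will be performed in the same manner as the primary analysis". All P "values will be two sided", and P "values <0.05 will be considered statistically significant".
- **Sample size estimation.** NT-proBNP is planned on the log ratio, with SD 0.80. No scale is stated for the secondary NT-proBNP analysis.

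**The concern.** Listing both value and change does no harm if the model contains the parameter's own baseline, because the two analyses then return the same treatment effect. The stated covariate list does not contain it. The two forms therefore become separate tests with separate estimates and P values, each judged at 0.05.

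Two things are at stake. First, a secondary parameter has two chances of being called significant, and when the two forms disagree the Trial endpoints section does not say which one to report. The trial is open-label, so a choice made once results are known would be open to challenge. Second, precision is lost: neither the unadjusted value nor the unadjusted change uses the baseline as efficiently as ANCOVA does.

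**Working it through.** **The plan's own figures.** The plan gives no error rate for the secondary endpoints, so none can be reproduced. Its sample size supplies two inputs (SD 0.80, and about 112 evaluable per arm from 125 × 0.9 = 112.5), so I checked it first. With margin ln 1.1 and true ratio 0.82, z = (ln 1.1 − ln 0.82)/(0.80 × √(2/112.5)) = 2.754. Power is Φ(2.754 − 1.960) = 0.786, close to the stated 80 %. The sample size does not bear on the point further.

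**Assumptions.** The document does not give the correlation ρ between baseline and 24-week value. I take equal variances and show a range of ρ.

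**Step 1: how far the two tests differ.** Let X be the baseline and Y the 24-week value, each with variance σ².

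- Cov(Y, Y−X) = σ²(1−ρ)
- SD(Y−X) = σ√(2(1−ρ))
- Corr(Y, Y−X) = √((1−ρ)/2)

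The more stable the parameter, the less the two tests agree.

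**Step 2: chance under no effect that at least one test has two-sided P<0.05.** This is 0.05 + 0.05 − P(both), with P(both) from the bivariate normal distribution.

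| ρ | correlation of tests | P(both) | P(at least one) |
|---|---|---|---|
| 0 | 0.707 | 0.0169 | 0.083 |
| 0.5 | 0.500 | 0.0093 | 0.091 |
| 0.7 | 0.387 | 0.0065 | 0.094 |
| 0.9 | 0.224 | 0.0038 | 0.096 |

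Two independent tests would give 1 − 0.95² = 0.0975. When at least one test is significant, only one of the two is in most cases: 1 − 0.0093/0.0907 = 90 % at ρ = 0.5, and 96 % at ρ = 0.9.

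**Step 3: HbA1c and LVEF.** Their dichotomised screening level is in the model. Simulating the ANCOVA (112 per arm, ρ from 0.5 to 0.9) with a two-level version of the outcome's own baseline gave about 0.080 to 0.096. The excess is somewhat smaller but does not vanish.

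**Step 4: effect of adding the continuous baseline.** Subtracting X from the outcome when X is already a covariate lowers the slope on X by exactly 1. The treatment coefficient and the residuals do not change, so value and change have the same t statistic. In simulation they never disagreed, and the rate for the pair returned to about 0.05 (0.048 to 0.055).

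**Step 5: precision.** The residual SD is σ for the value, σ√(2(1−ρ)) for the change and σ√(1−ρ²) with the baseline as covariate. For a true effect of 0.3 SD and 112.5 per arm, two-sided power is:

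| ρ | value | change | baseline-adjusted |
|---|---|---|---|
| 0.5 | 0.61 | 0.61 | 0.74 |
| 0.8 | 0.61 | 0.94 | 0.96 |
| 0.9 | 0.61 | >0.99 | >0.99 |

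For log NT-proBNP at a ratio of 0.82, assume a log-baseline SD of 0.9 or 1.2, which is not in the document. A log-ratio SD of 0.80 then implies ρ = 1 − 0.64/(2 × 0.81) = 0.605 or 1 − 0.64/(2 × 1.44) = 0.778. The residual SD falls from 0.80 to 0.9 × √(1 − 0.605²) = 0.717 or 1.2 × √(1 − 0.778²) = 0.754. With 112 per arm, z = 0.198/(SD × 0.1336) rises from 1.86 to 2.07 or 1.97, and power from about 46 % to about 54 % or 50 %. This is power to detect a difference, used only to measure precision. It is not the power of the non-inferiority test.

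**Step 6: NT-proBNP, if the secondary analysis were run in pg/mL.** Lognormal simulation with 112 per arm and the same two baseline SDs: at a true ratio of 0.82, the absolute-change difference has the opposite sign to the log-ratio difference in about 9 % (SD 0.9) and 15 % (SD 1.2) of trials.

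**The case against.** Several objections have force.

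- **Priority between the forms.** A reader of the Trial endpoints section might infer that nothing ranks value against change. The Abstract does: its key secondary endpoints are changes from baseline, for most of the parameters listed. What remains is a broader list in Trial endpoints that should be aligned with the Abstract.
- **The trial's error rate.** A reader might infer that the false-positive rate of the trial nearly doubles. It does not. The figure is per parameter, for secondary endpoints that carry no confirmatory claim. Non-inferiority is decided on percent change in NT-proBNP, and a secondary NT-proBNP result cannot alter it.
- **Raw scale.** A reader might infer that the secondary NT-proBNP analysis will be in pg/mL. The article states no scale. The sample size uses the log ratio and the secondary analysis follows the primary, so the 9 to 15 % figure is conditional.
- **Skewness.** The provision for "Wilcoxon rank sum tests for continuous variables with a skewed distribution" concerns patient characteristics. Silence on transforming skewed secondary endpoints is ordinary condensation in an article, and an analysis plan would normally settle it. It is not an error here.
- **Coverage.** The calculation describes continuous parameters. It does not cover NYHA class or clinical events, and the exploratory biomarkers have no duplication.
- **A derivative point.** If a baseline covariate were added to the primary model, the clause carrying the same method to the secondary endpoints might bring the fix with it. That is fair, but the article names its covariates and does not include any parameter's own continuous baseline. It would still have to be said that each parameter takes its own.

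What survives all of these is that the stated endpoint list and the stated covariate list together produce two different tests per continuous parameter, and that a covariate already collected removes the difference.

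**Conclusion.** The point holds as a free improvement. For each continuous secondary parameter, the planned value and change analyses are different tests. The chance that at least one is significant under no effect is about 8 to 10 % rather than 5 %. That rests on equal variances and an assumed correlation of 0 to 0.9; for HbA1c and LVEF the simulated rate is about 8.0 to 9.6 %. The primary test's error rate is not affected. The gain in precision from adding the baseline also depends on the correlation: it is largest against the value analysis when the correlation is high, and small against the change analysis in that case.

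The documents do not support removing the secondary NT-proBNP endpoint. That would be a reporting preference. For that endpoint it is enough to state the scale.

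**What to change.** 1. In the Analysis plan section (or the statistical analysis plan), add each continuous parameter's own baseline value as a covariate, alongside the three stratification factors.
2. Align the secondary list in Trial endpoints with the Abstract, so that one inferential result is reported per parameter. With the baseline in the model, value and change share the same treatment effect and P value, so the form can be chosen for readability.
3. For NT-proBNP, state that the log scale already assumed for the sample size is used.

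The cost is wording only. The Measurements section already provides baseline NT-proBNP, quality of life and echocardiography, with weight, blood pressure, and blood and urine tests at each visit. The article says the statistical analysis plan is to be written before recruitment ends and the database is locked, so the change fits the planned timetable. No sample size or visit change follows.
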